In the present study, we modified the traditional SMS formula used for CVD (ginseng, Ophiopogon japonicus, and Schisandra chinensis) based on clinical experience, classic texts, and experiment findings. We removed ginseng and added Platycodon grandiflorus and Pueraria lobata as well as Dioscorea opposita and Coix lacrymajobi to stimulate digestive functions. The formula consisting of **Pueraria lobata (5.33g), Platycodon grandiflorus (5.33g), Ophiopogon japonicus (5.33g), Dioscorea opposita (2.67g), Coix lacrymajobi (2.67g), and Schisandra chinensis (2.67g) (total 24g; unit g/day)** is referred to as saengmaeksangagambang (modified SMS), and this prescription is empirically used at Kyung Hee Bi, Che, Dam Korean Medicine Clinic to treat CVD or autonomic nervous system symptoms. The ingredients are prepared as a decoction with alcohol as a solvent, in accordance with the concept of principal and ministerial inversion in Korean medical classic for use at the clinic. We will conduct an observational study using this prescription.

1. Effects of modified SMS in an animal study

There was an animal study showing that SMS was effective in BP regulation. In mice with normal BP, BP was lowered in the high-dose group, and local blood flow also increased dose-dependently in mice with normal BP given SMS. In a preclinical trial, SMS led to reduced NO production in rat aortic VSMC treated with TNF-α + IFN-γ, increased cell viability, and reduced iNOS protein and mRNA production.

A preclinical trial on the use of modified SMS (the investigational product of our trial) confirmed suppression of increased BP. A study on the effects of a three-week modified SMS regimen in mice with HTN induced with L-NAME showed that the BP was lowered to near-normal levels in the SMS group compared to the non-SMS group. In particular, ethanolic extract of modified SMS was more effective than water extract of modified SMS (Figures 2, 3).

In light of the result of the previously mentioned preclinical trial, where SMS reduced the production of vasoconstrictors in VSMC in mice, modified SMS is believed to be a promising therapeutic option for HTN.

[figure not shown]

Figure 2

Graphs summarize systolic BP(A), and diastolic BP(B) (a,***p<0.001 Before L-NAME vs. After L-NAME ; b, *** p<0.001 After Normal vs. After L-NAME). BP was measured using the tail-cuff method. Results are expressed as the mean ±S.E. (n=6 mice per group). Before, L-NAME non-treatment; After, L-NAME treated.

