- (Visit) Patients who take herbal medicine prescribed by Kyung Hee Bi, Che, Dam Korean Medicine Clinic are instructed to make f/u visits every 4 weeks for monitoring of AEs and clinical progress. In case of AEs, additional visits may be necessary.

1. Standard protocol tests

- The Standard management protocol at Kyung Hee Bi, Che, Dam Korean Medicine Clinic involves performing 3D BP waveform test and blood tests on patients taking herbal medicines every four weeks. In the present study, only patients taking modified SMS were enrolled. However, additional tests may be performed in cases of AEs.

1. Study intervention: administration of modified SMS per standard protocol

In the present study, we modified the traditional SMS formula used for CVD (ginseng, Ophiopogon japonicus, and Schisandra chinensis) based on clinical experience, classic texts, and experiment findings. We removed ginseng and added Platycodon grandiflorus and Pueraria lobata as well as Dioscorea opposita and Coix lacrymajobi to stimulate digestive functions. The formula consisting of **Pueraria lobata (5.33g), Platycodon grandiflorus (5.33g), Ophiopogon japonicus (5.33g), Dioscorea opposita (2.67g), Coix lacrymajobi (2.67g), and Schisandra chinensis (2.67g) (total 24g; unit g/day)** is referred to as saengmaeksangagambang (modified SMS). This is one of the unique empirical prescriptions used at Kyung Hee Bi, Che, Dam Korean Medicine Clinic. Although in actual practice at Kyung Hee Bi, Che, Dam Korean Medicine Clinic, **certain ingredients may be removed, doses may be adjusted, or other interventions such as acupuncture, may be added depending on the symptoms and disease being treated, such cases were excluded from the analysis in this study.**

- Patients take a 60-mL 70% alcohol-soaked decoction of the modified SMS formula prepared by Kyung Hee Bi, Che, Dam Korean Medicine Clinic twice daily before meals or between meals
- Dispensing of medicine on Visit 1, Visit 2: [number of days until next scheduled visit date (standard 28 days, maximum 35 days) + 3 days]* 2 packs. A standard of 62 packs, up to 76 packs, are packaged in a box or pack, labeled with the patient’s information.
- Participants will return unused medicine at the subsequent visit.
- Returned unused medications will be stored separately for each patient in a box/pack.
- At completion of trial, returned medicines will be disposed of following the facility’s medication disposal procedures.

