- Dose per pack: modified SMS: each pack contains 60 mL containing Pueraria lobata (5.33g), Platycodon grandiflorus (5.33g), Ophiopogon japonicus (5.33g), Dioscorea opposita (2.67g), Coix lacrymajobi (2.67g), and Schisandra chinensis (2.67g) (total 24g; unit g/day).
- Dosage: oral; 2 packs a day
- Treatment period: 8 weeks (56 days) (f/u every 4 weeks)
- Permitted concomitant treatments: Given the observational nature of this study, we will not limit any concomitant treatments and medications while undergoing the SMS regimen, and concomitant treatments will be documented.
  * Use/non-use of antihypertensive drugs will be documented.
  * If antihypertensive drugs are being used, patients are informed to notify the investigator upon changes in the dose and dosage of the drug.
  * Patients are informed to maintain their normal lifestyle, including exercise and diet.
- The dose and dosage of modified SMS used in this trial are identical to those used in actual practice at Kyung Hee Bi, Che, Dam Korean Medicine Clinic.

|  | | |
| --- | --- | --- |
| [figure not shown] | [figure not shown] | [figure not shown] |
| Cold extraction | Vacuum concentration | Concentrate |

Figure 5. Preparation facilities at Kyung Hee Bi, Che, Dam Korean Medicine Clinic and appearance of concentrates

1. Additional interventions, visits, and tests required for study participation per the purpose

The Standard management protocol at Kyung Hee Bi, Che, Dam Korean Medicine Clinic involves performing 3D BP waveform test and blood tests on patients taking herbal medicines every four weeks. In the present study, only patients taking modified SMS were enrolled. **Thus, there are no additional interventions required for participation in this study**

**In case of an adverse event, f/u is needed until the adverse event is resolved. In such cases, additional visits may be necessary.**

In case of an adverse event, additional tests, such as kidney function test, liver function test, and complete blood count, may be performed.

1. Control group, randomization, blinding

This is a single-group study without a control group, so randomization and blinding are not applicable.

1. Summary of study timeline (anticipated duration, place, staff in charge, study procedure)

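### The protocol gives 24 g of herb both as the daily total and as the content of each of two daily packs, so the documented herb amount is uncertain by a factor of two

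*Protocol*

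**What the plan says.** The herb content appears three times in the protocol.

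- **Study Background, definition of modified SMS.** The list of six ingredients ends "Coix lacrymajobi (2.67g), and Schisandra chinensis (2.67g) (total 24g; unit g/day) is referred to as saengmaeksangagambang (modified SMS), and this prescription is empirically used" at the clinic. This is a daily amount.
- **Method, Study intervention (opening paragraph).** The same list is repeated and ends "Dioscorea opposita (2.67g), Coix lacrymajobi (2.67g), and Schisandra chinensis (2.67g) (total 24g; unit g/day) is referred to as saengmaeksangagambang (modified SMS". This is again a daily amount.
- **Method, Study intervention (dose-per-pack line).** Here the same amounts are the content of one pack: "each pack contains 60 mL containing Pueraria lobata (5.33g), Platycodon grandiflorus (5.33g), Ophiopogon japonicus (5.33g", followed by "Dioscorea opposita (2.67g), Coix lacrymajobi (2.67g), and Schisandra chinensis (2.67g) (total 24g; unit g/day". The unit is still per day, although the line describes a pack.

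The line after that reads "Dosage: oral; 2 packs a day". The same section gives the intake as "Patients take a 60-mL 70% alcohol-soaked decoction of the modified SMS formula", twice daily, and sets dispensing at "number of days until next scheduled visit date (standard 28 days, maximum 35 days) + 3 days]* 2 packs", which it works out as 62 packs as standard and 76 at most. The treatment period is 56 days.

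The section also says that the trial uses the same dose and dosage as the clinic's ordinary practice. It gives no separate gram figure for that practice.

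**The concern.** The three statements and the two-pack instruction cannot all be true. If each pack holds 24 g, two packs are not 24 g a day. If the day's total is 24 g, a pack does not hold the listed amounts.

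Modified SMS is the only intervention, and the stated purpose is to explore its safety and its effect on blood pressure. The Method and Outcome sections add that the data are meant to inform later studies, including the feasibility of a randomised trial. The results will therefore be read as belonging to a stated amount of herb, and the protocol states two.

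The stated formula also has a role inside the study. Under Study intervention, patients whose formula or dose is altered are left out of the analysis. The discontinuation criteria list a change of prescription, and Table 2 schedules monitoring of adherence and dosage. Anyone checking these points in grams from the protocol alone has no single reference figure.

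**Working it through.** **Inputs (all from the protocol)**

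- Three ingredients at 5.33 g and three at 2.67 g (Study Background; Study intervention, twice).
- Two packs a day, 60 mL each (Study intervention).
- Dispensing: days to the next visit (28 standard, 35 maximum) plus 3, times 2 packs.
- Treatment period: 56 days.

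**Step 1: reproduce the stated total.** 3 × 5.33 + 3 × 2.67 = 15.99 + 8.01 = 24.00 g. The figure of 24 g is not an addition or rounding error.

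**Step 2: check the pack count.** (28 + 3) × 2 = 62 and (35 + 3) × 2 = 76. Both match the protocol. Two packs of 60 mL make 120 mL a day, which agrees with 60 mL taken twice daily. The number of packs and the volume are not in doubt.

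**Step 3: work out both readings.**

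| | 24 g is the daily total | 24 g is the content of each pack |
| --- | --- | --- |
| Herb per pack | 24 / 2 = 12 g | 24 g |
| Herb per day | 24 g | 2 × 24 = 48 g |
| Herb over 56 days, all packs taken | 56 × 24 = 1,344 g | 56 × 48 = 2,688 g |
| Conflicts with | the listed pack contents | both definitions, and the unit in the pack line |

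The ratio is 48 / 24 = 2. The 56-day totals assume full adherence and add nothing beyond that ratio.

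**Step 4: look for text that decides between them.** No section gives 12 g per pack or 48 g per day, and none explains the double use of 24 g. The statement about ordinary practice does not help, because the only gram figures given for the product are the ones in conflict.

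**The case against.** The strongest reply is that this is a drafting slip with little practical effect. The same ingredient string, daily unit included, appears in all three places, which is compatible with its having been copied into the pack line. The study has one site. That site prepares the product itself and has long used the prescription, so it may well know what goes into a pack. What participants are told to take is clear and consistent. No planned analysis uses grams: the primary outcome is the change in mean seated systolic pressure from visit 1 to visit 3, and no dose-response analysis is stated.

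Most of this stands, and it rules out several stronger readings.

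- A reader might infer that the site cannot tell what to prepare, or that participants could receive different amounts. The documents do not show this. The defect is in what the protocol records.
- A reader might infer that a wrong dose will pass into a planned randomised trial. The protocol mentions the feasibility of a future trial and data for later studies, but carries no dose forward.
- A reader might infer that pack labels or case report forms carry the wrong figure. The protocol says only that packs bear the patient's information, and shows no gram figure on either.
- A reader might conclude that the results would be invalid. They would still describe the product as dispensed.

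The reply does not remove the contradiction. That the daily formula was copied into the pack line is an inference. The sentence as written states pack contents, and a reader of the protocol cannot correct it without information from outside the document.

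**Conclusion.** The concern holds as an internal inconsistency in the documented herb content; it is not a question of design choice. The text supports 24 g and 48 g a day (12 g and 24 g a pack), a factor of exactly two, and nothing in the protocol decides between them. Packs per day, volume, sample size and planned tests are unaffected.

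The point is more than clerical because the disputed figure describes the sole intervention, and so the exposure to which the blood pressure and safety findings will be attributed and which later studies would cite.

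The conclusion rests only on the protocol's own figures and on reading the pack line literally. It takes no position on which amount is correct.

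**What to change.** The sponsor and investigator should reconcile the definition in the Study Background, the opening paragraph of Study intervention and the dose-per-pack line against the clinic's preparation record. Amount per pack, packs per day and total per day should then agree, and each line should carry its own unit, per pack or per day. The same figures should be used wherever the dose is recorded or reported. Which amount is right is for the sponsor and investigator to confirm.

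The cost is a check of the preparation record and a wording change in up to three places. No sample-size or analysis change follows. The correction is best made before dispensing; if that has passed, the preparation record can still be used to correct the description when results are reported.

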[figure not shown]

Figure 3

Graphs summarize systolic BP(A), and diastolic BP(B) in groups of Nor, L-Con, L+mSaengmaeksan_W, and L+mSaengmaeksan_E. Treatment with mSaengmaeksan_E ameliorated HTN in the L-Congroup (a, ***p＜0.001 Norvs. L-Con; b, ***p＜0.001 L-Convs. L+mSaengmaeksan_E). Results are expressed as the mean ±S.E. (n=6 mice per group). Nor, normal; L-Con, L_NAME control; L+mSaengmaeksan_W, mSaengmaeksan water extract treated L-NAME control groups; L+mSaengmaeksan_E, mSaengmaeksan ethanol extract treated L-NAME control groups.

1. Purpose of study

This study is an exploratory observational study that aims to explore the safety and BP-lowering effects of modified SMS and to collect HTN-related clinical parameters by comparing before and after administration of modified SMS, an herbal medicine prepared and prescribed at Kyung Hee Bi, Che, Dam Korean Medicine Clinic for the treatment of HTN.

1. Names and positions of principal investigator, co-investigators, and sub-investigators
2. Principal investigator (PI)

| Name | Affiliation | Job position | Contact information | Roles |
| --- | --- | --- | --- | --- |
| [name] | Kyung Hee Bi,Che,Dam Korean Medicine Clinic | Director | [name] / [contact] | PI, recruit and enroll participants, provide information about study and obtain consent, collect data, measure observation parameters, and perform tests |

1. Co-investigators

| Name | Affiliation | Job position | | Contact information | | Roles | |  |
| --- | --- | --- | --- | --- | --- | --- | --- | --- |
| Name | Affiliation | | Job position | | Contact information | | Roles | |
| [name] | Kyung Hee Bichedam Korean Medicine Clinic | | Research assistant | | [name] / [contact] | | Study administration and trial assistance | |
| [name] | Korean Institute of Oriental Medicine | | Principal researcher | | [contact]/[contact] | | Study design | |
| [name] | Korean Institute of Oriental Medicine | | Principal researcher | | [contact]/[contact] | | Study design | |
| [name] | Korean Institute of Oriental Medicine | | Principal researcher | | [contact]/[contact] | | Develop data analysis and statistical analysis methods | |
| [name] | Korean Institute of Oriental Medicine | | Technical researcher | | [contact]/[contact] | | Monitors | |

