A study questionnaire will be used to obtain data, and a total of five test parameters will be monitored. The questionnaire and tests will be performed at every visit, and it will take about 30 minutes. The questionnaire and tests will be performed at Kyung Hee Bi, Che, Dam Korean Medicine Clinic, and the PI will be in charge of distributing and collecting the questionnaire and performing tests.

| Item | Screening and enrollment | Treatment phase | | F/U |
| --- | --- | --- | --- | --- |
|  |  | 4wks | 8wks | 12wks |
| Visit | Visit 1 | Visit 2 | Visit 3 | Visit 4 |
| Visit window | 0주 | Week 4 (±7 days) | Week 8  (±7 days) | Week 12  (±7 days) |
| Informed consent | ○ |  |  |  |
| Sociodemographic information | ○ |  |  |  |
| VS and physical examination | ○ | ● | ● |  |
| Compliance with pre-visit instructions | ○ | ● | ● |  |
| Medical history·treatment history·medication history | ○ |  |  |  |
| Inclusion and exclusion criteria | ○ |  |  |  |
| Blood test | ● | ● | ● |  |
| BP and pulse measurement | ○ | ● | ● |  |
| 3D BP waveform test | ● | ● | ● |  |
| European Quality of Life Five Dimension Five Level Scale (EQ-5D-5L) | ● | ● | ● |  |
| Modified SMS prescription and dispensing | ● | ● |  |  |
| Monitoring of herbal medicine adherence and dosage |  | ● | ● |  |
| Monitoring of AEs |  | ● | ● | ● |
| Changes in Medical history·treatment history·medication history ** |  | ● | ● | ● |
| Conclusion of case* |  |  |  | ● |

Table 2. Summary of study data collected by timeline

* Conclusion of case: collected after visits are completed or participant is discontinued

** Changes in Medical history·treatment history·medication history: Collect information upon changes in Medical history·treatment history·medication history since the visit

● Tests performed only on those who qualify per the inclusion/exclusion criteria

eCRF will be identical to the paper-based CRF, and the Mytrial program at NIKOM will be used to establish the eCRF.

Modified intervention records: if the treatment interventions are changed mid-way, the changes will be recorded in the modified intervention record section of the CRF.

Concomitant drugs and treatment: Concomitant drugs and treatment will be recorded in the respective section in the CRF.

1. Management of human-derived materials

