6. BP response rate at end of treatment (visit 3) compared to the baseline (visit 1) (percentage of patients who had MSSBP drop by 20 mmHg or more or MSDBP drop by 10 mmHg or more)
7. Amount of change in individual parameters on 3D pulse wave imaging at visits 2 and 3 compared to the baseline (visit 1)
8. Amount of change in EQ-5D-5L score at visits 2 and 3 compared to the baseline (visit 1)
9. Outcome evaluation criteria

This study is a prospective study conducted to present data for subsequent studies on modified SMS; the purpose is not to determine the clinical efficacy of the drug, but rather, to explore and collect preliminary data.

However, for the statistical analysis in this study, we will present the degree of improvement in the continuous variables using descriptive statistics.

Efficacy is determined based on the improvement of MSSBP, 3D pulse wave imaging parameters, and Eq-5D-5L score at visits 2 and 3 compared to the baseline, and the percentage of patients who have achieved such improvements is presented. However, because the study is an exploratory study without a control group, there are limitations in determining efficacy.

As this study observes effects during a routine treatment protocol, we will collect the following data that may potentially influence BP and control for them in the analysis.

* Collection of information about the use of antihypertensive drugs.
* If the patient is using antihypertensive medication, they are informed to notify the investigator upon changes in the dose and dosage of the drug.
* Patients are informed to maintain their normal lifestyle, including exercise and diet

ANCOVA is performed with sociodemographic variables that may affect HTN, namely sex, age, BMI, duration of HTN, comorbidity, BP at initial visit, use of antihypertensive medication, and types of drugs, controlled for as covariates.

1. Anticipated AEs, precautions, and measures to address them
2. Additional AEs anticipated as a result of participation in observational study

In this observational study, the same process used in the standard treatment protocol is used, which involves taking modified SMS, performing tests and questionnaires, and documenting them in the CRF. Thus, there are no additional tests or interventions performed other than those included in the standard treatment process; for this reason, there are no other anticipated AEs in addition to the AEs that may occur during the standard treatment process.

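### The EQ-5D-5L is handed out and collected by the PI, and its baseline comes after BP qualification, which leaves an uncontrolled self-report outcome open to avoidable reporting bias of unknown size

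*Protocol*

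**What the plan says.** **Who handles the form.** The section summarising the study timeline states that "the PI will be in charge of distributing and collecting the questionnaire and performing tests". The table of investigators lists the PI's duties as "PI, recruit and enroll participants, provide information about study and obtain consent, collect data, measure observation parameters, and perform tests". A research assistant at the same clinic is listed for "Study administration and trial assistance".

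**When it is completed.** In Table 2 the row "BP and pulse measurement" and the eligibility check carry an open circle at visit 1. The EQ-5D-5L carries a filled circle at visits 1, 2 and 3, and nothing at visit 4. The legend defines the filled circle as "Tests performed only on those who qualify per the inclusion/exclusion criteria". For visits 2 and 3 no order between the form, the cuff reading and the 3D pulse-wave test is given.

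**How it is used.** Change in EQ-5D-5L from visit 1 to visits 2 and 3 is a secondary outcome. Section 13.C adds: "Efficacy is determined based on the improvement of MSSBP, 3D pulse wave imaging parameters, and Eq-5D-5L score at visits 2 and 3". Continuous efficacy variables are tested by paired t-test or Wilcoxon signed rank test, two-sided at 5%. There is no control group and no blinding.

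**The concern.** The EQ-5D-5L is pure self-report, so the circumstances in which it is filled in can move the score. Two features of the stated procedure could move it in the product's favour.

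- **Labelling.** At visit 1 every enrolled patient has just had a BP reading high enough to qualify. If that colours the answers, the baseline score is lowered. Later readings are not selected for being high, so the effect need not cancel in the change score.
- **Courtesy.** The patient returns the form to the person who recruited them and takes the measurements. A constant wish to please would cancel between visits. Any part that grows once treatment has begun would appear as improvement.

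No comparison arm absorbs either effect. The study exists to supply preliminary data for later trials, so a distorted EQ-5D-5L change could be carried into their planning. Because this is a matter of data collection, no later analysis can repair it.

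**Working it through.** **1. Order at visit 1.** Eligibility requires a mean sitting SBP of 140 to below 180 mmHg without antihypertensive drugs, or 130 to below 180 mmHg with them (inclusion criteria). A filled-circle item is done only in patients who qualify. Qualifying needs the BP reading, so the baseline EQ-5D-5L comes after it. This follows from the table's own legend.

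**2. Order at visits 2 and 3.** All items carry the same symbol, and the text gives no sequence. The section on measurement items lists the EQ-5D-5L after cuff BP and after the 3D pulse-wave test, which itself reports SBP and DBP. A list is not a stated order, but nothing puts the form first.

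**3. Number analysed.** The plan's own sample-size figure reproduces: 20 / (1 − 0.33) = 29.85, rounded up to 30. The EQ-5D-5L analysis would thus use between about 20 patients (completers) and 30 (everyone, with the planned LOCF).

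**4. Sensitivity illustration.** The protocol gives no SD, expected change or bias size for the EQ-5D-5L, so what follows is assumed. Let the true change be zero, and let d be a systematic reporting shift in units of the SD of the change score. As an example, an index shift of 0.02 with an SD of change of 0.10 gives d = 0.02 / 0.10 = 0.2, and a shift of 0.05 gives d = 0.5.

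The paired t statistic then follows a noncentral t distribution with n − 1 degrees of freedom and noncentrality d√n. The rejection rate is

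P(T > t₀.₉₇₅,ₙ₋₁) + P(T < −t₀.₉₇₅,ₙ₋₁).

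For d = 0.2 the noncentrality is 0.2 × √20 = 0.89 at n=20 and 0.2 × √30 = 1.10 at n=30. For d = 0.5 it is 2.24 and 2.74.

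| Assumed shift d (SD) | Rejection, n=20 | Rejection, n=30 |
|---|---|---|
| 0 | 5.0% | 5.0% |
| 0.1 | 7.1% | 8.3% |
| 0.2 | 13.6% | 18.5% |
| 0.3 | 24.7% | 35.5% |
| 0.5 | 56.5% | 75.4% |

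The table shows how a one-sample change test reacts to a constant shift from any source. It does not say how much shift the order of the form or its collector would produce.

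**The case against.** Most of the case on the other side limits how far the point reaches, and much of it stands.

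- **Bias is not shown to be present.** A reader might infer that the EQ-5D-5L change is biased. The documents support only a risk. No text says the reading is told to the patient before the form, although being found eligible on published BP criteria conveys much the same news.
- **Many patients are already labelled.** Recruits are described as patients with hypertension, and those on antihypertensive drugs are admitted. For them a raised reading is hardly news. The same-day effect is most plausible in untreated patients.
- **Reordering cannot remove both biases.** Courtesy bias depends on who handles the form. The research assistant works at the same clinic, and patients know what they are taking. Some of the effect remains under any arrangement at this site.
- **The PI as prescriber is an inference.** The protocol calls the product "an herbal medicine prepared and prescribed at Kyung Hee Bi, Che, Dam Korean Medicine Clinic for the treatment of HTN" and the PI directs that clinic, but it does not state that the PI prescribes. Being in charge of the form also does not exclude delegation.
- **The outcome is secondary and the study exploratory.** Section 13.C says that establishing clinical efficacy is not the purpose, and it concedes the limits of having no control group. The primary outcome is cuff SBP, and no decision rule rests on the EQ-5D-5L.

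The last point sets the importance of the finding but does not answer it. With no control arm, the handling of the form is one of the few protections available.

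**Conclusion.** The point holds as a low-cost improvement to a secondary outcome. It is not an error or a contradiction in the plan. Three things are firm: the PI is in charge of the form, the baseline form follows BP qualification, and no order is fixed at visits 2 and 3. Together they expose an uncontrolled self-report outcome to possible labelling and courtesy bias.

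The size is unknown. A reader might take 13.6% to 75.4% as this study's false-positive rate for the EQ-5D-5L. The documents do not support that, because the range rests wholly on assumed shifts of 0.2 to 0.5 SD. A shift of 0.1 SD gives only 7.1% to 8.3%. Nor do the documents allow an estimate of how much of any shift the fix would take away. Other sources of before-after change, such as expectation and concomitant treatment, would remain.

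**What to change.** In the section summarising the study timeline:

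1. Name the research assistant, already listed among the co-investigators, as the person who hands out and collects the EQ-5D-5L.
2. State that the patient completes it alone, after consent at visit 1 and before any cuff BP or pulse-wave reading at visits 1, 2 and 3.
3. In Table 2, change the visit 1 mark for the EQ-5D-5L from a filled to an open circle.

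If the order cannot be changed, report it as a limitation of the EQ-5D-5L result.

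**Cost.** No new staff or test is needed. Consented patients who then fail screening would also fill in the form, which the protocol puts at 5 minutes. The protocol already counts the EQ-5D-5L among its routine-care information. Done first, the form also precedes the 15-minute rest before BP measurement and does not disturb it. The change reduces the exposure to reporting bias but does not remove it.
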